| Study Design The research aims will be addressed with a matched cohort study design.  Two cohorts will be assembled from the CPRD GOLD primary care database:  (1) The exposed cohort will include women diagnosed with a breast cancer (list of Read codes available in appendix 2) after at least 12 months of uninterrupted up-to-standard follow-up in CPRD (to ensure that the breast cancer is an incident event).  (2) A comparison cohort will be assembled by randomly selecting, for each woman with a breast cancer diagnosis, up to 4 women of similar age (3-year range), attending the same GP practice and with at least 12 months of uninterrupted up-to-standard data quality for research, but with no history of cancer at the date of the breast cancer diagnosis of the matched breast cancer patient.  The index date will be the date of breast cancer diagnosis for the exposed group; comparison patients will take the same index date as their exposed match. Please see section L for more details.  Inclusion criteria for both cohorts are: female sex, aged ≥18 years, and having a clinical record with at least 12 months of uninterrupted up-to-standard data quality for research (as measured by CPRD) before the breast cancer diagnosis date (to ensure the cancer record represents incident disease). Exclusions will be the diagnosis of severe mental illness (i.e. organic mental disorder, mental disorders due to substances, schizophrenia, delusional disorders, or manic or bipolar episodes), having a history of the specified mental health outcome in the year before index date; and having had a diagnosis of any other cancer prior to the index date.  All women will be followed from the index date until the earliest date of: outcome observed, a cancer diagnosis, death recorded, transference out of the practice; last data collection for the practice.  Matching will allow close control of key covariates, include GP practice that is difficult to adjust for in a statistical model (too many levels), and has the practical advantage of reducing the size of the comparison group (which might otherwise include several million women) by restricting to the most relevant comparison patients. |

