| Definition of the Study population Breast cancer cohort  The study population will consist of all adult women recorded in the CPRD GOLD primary care database as having had an incident breast cancer (Read codes provided in appendix 2) diagnosed during up-to-standard follow-up and prior to the most recent version of the CPRD GOLD primary care database available after all approvals have been obtained.  Inclusion criteria:   1. Female sex, aged ≥18 years; 2. Recorded with a breast cancer diagnosis during CPRD follow-up; 3. Clinical record with at least 12 months of uninterrupted up-to-standard data quality for research (as measured by CPRD) before the breast cancer diagnosis date (to ensure the cancer record represents incident disease).   Exclusion criteria:   1. Diagnosis of severe mental illness before the breast cancer diagnosis (i.e. organic mental disorder, mental disorders due to substances, schizophrenia, delusional disorders, or manic or bipolar episodes) (a provisional list of Read codes was defined for feasibility counts); 2. History of the specified mental health outcome in analysis in the year before the breast cancer diagnosis (list of Read codes to be defined in objective 1 of this study); 3. Diagnosis of any other cancer prior to breast cancer (Read codes available from Ranopa et al. [14]). |
| Selection of comparison group(s) or controls Non-cancer comparison cohort  A comparison cohort will be assembled by randomly selecting, for each index case, up to 4 women of similar age (3-year range), attending the same GP practice, but with no history of cancer at the index date. Matching will also consider the eligibility of the patients’ data for linkage, to ensure that matched-sets have the same probability of having had the information recorded when conducting sub-set analysis using linked data. Controls will be selected using nearest neighbour matching methods without replacement [29]. Women in the non-cancer comparison cohort who meet one or more exclusion criteria will be excluded, as well as their index case.  Women diagnosed with breast cancer during the follow up period will be censored from the unexposed group at the date of the cancer diagnosis, but will be eligible to separately contribute in the exposed group from this date (with corresponding unexposed matches). |

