| Exposures, Outcomes and CovariatesExposure: breast cancer Women will be considered exposed at the day of the breast cancer diagnosis (index date), denoted by the first entry of one or more of the Read codes provided in appendix 2. Primary outcomes: anxiety and depression To our knowledge, there is no validated list of Read codes to identify anxiety and depression in the CPRD GOLD primary care database. Algorithms will be developed and tested to identify anxiety and depression cases in CPRD. The algorithms will be chiefly determined by clinical diagnoses of anxiety and depression registered in the EHR with Read codes, and supplemented with information from drug prescriptions, referrals, and symptoms (if deemed suitable). Please see section N, plan of analysis for specific aim 1, for more details on the construction and validation of algorithms. Secondary outcomes: fatigue, mild cognitive impairment, pain, sleep disturbance, sexual dysfunction, and fatal and non-fatal self-harm Similarly, we will develop and test outcome-specific algorithms that identify events using a hierarchy of data on clinical diagnoses, prescriptions, referrals and symptoms.  In sensitivity analysis, we will consider linked data (see section J for data linkage requested) to develop more precise definitions of the outcomes, when possible. For example, two definitions of suicide will be considered: (1) considering Read codes only to identify suicides in CPRD; (2) considering Read codes for suicide as well as death registration data where suicide was recorded as primary cause of death (ICD-10 codes provided in appendix 3) Covariates Variables considered as potential confounders or effect modifiers of the association between breast cancer history and anxiety and depression (the primary outcomes of this study) are described below. The directed, acyclic graph (DAG) in appendix 4 explicitly describes the assumptions of the causal relations between the variables that underpin the choice. Please refer to the data analysis (section N) for details on which variables will be considered for sensitivity analyses only. *Potential confounders*  - Age at diagnosis (categorical variable, in 10-year age bands)   Defined as the absolute difference between the year of breast cancer diagnosis and year of birth. Age is a strong risk factor for breast cancer and for mental disorders.   - Alcohol drinking habits at diagnosis (categorical variable: current drinker, former drinker, never drinker)   Excess alcohol drinking is a well-established risk factor for breast cancer [30], besides being positively associated with anxiety and depression [31-33]. The most recent data on alcohol drinking habits prior to index date will be used in analysis. Current drinking will be further sub-divided into high, moderate, low or unknown intake of alcohol.   - Body mass index at diagnosis (categorical variable: underweight, normal weight, overweight, obesity class I, obesity class II and above)   Calculated as BMI=(weight/height^2^). Higher body mass index is protective against breast cancer in pre-menopausal women, but a risk factor for breast cancer post-menopause [34]. Obesity increases the risk of anxiety and depression [35, 36]. The most recent recording of BMI prior to index date will be used in analysis. The BMI values will be categorised into 5 categories: <18.5 kg/m^2^ (underweight), 18.5-24.9 kg/m^2^ (normal weight), 25.0-29.9 kg/m^2^ (overweight), 30.0-34.9 kg/m^2^ (obesity class I), ≥35.0 kg/m^2^ (obesity class II and above). Read codes for body weight categories recorded in the year prior to the breast cancer diagnosed will be considered to supplement missing information for this variable.   - Calendar period of diagnosis (categorical variable: ≤1994; 1995-1999; 2000-2004; 2005-2009; 2010-2014; >2014)   Even though calendar time *per se* does not change the risk of breast cancer, the risk of being diagnosed with breast cancer changed over time, probably due to increase awareness of the disease along with widespread use of mammography to screen for breast cancer. Time has also contributed for mental disorders being more likely to be diagnosed, due to raises awareness and increased recognition of the importance of mental disorders among health care professionals.   - Diabetes mellitus (dichotomous variable: yes/no)   Diabetes mellitus has been associated with an increased risk of breast cancer [37] and depression [38]. Algorithms previously defined elsewhere will be applied to identify patients with diabetes mellitus in the CPRD GOLD primary care database [39, 40].   - Level of deprivation (categorical variable: quintiles of patient-level IMD).   The IMD is an ecological measure of deprivation for small areas in England that combines information from seven domains (income, employment, education, health deprivation, crime, barriers to housing, and living environment), and ranks the small area from 1 (most deprived) to 32,844 (least deprived). Patients will be categorised in quintiles of IMD, with quintile 1 representing those least deprived and quintile 5 those most deprived.   - Menopausal status (dichotomous variable: premenopausal/postmenopausal)   Menopausal status is a potential confounder of the association between breast cancer history and depression, as the risk of breast cancer increases with menopause [30], and so does the risk of depression [42]. However, information on menopausal status is not easily available in the CPRD database. We will therefore produce results stratified by an age cut-off, as a proxy of the menopausal status of the women. The cut-off will be the mean/median age at natural menopause in the UK.   - Smoking history at diagnosis (categorical variable: current smoker, former smoker, never smoker)   Information on Read codes available on the data will be used to classify patients by smoking history. The most recent data on smoking prior to index date will be used in analysis. *Potential effect modifiers*  - Living alone (dichotomous variable: yes/no)   Ascertained from the CPRD GOLD primary care data using Read codes (list provided in [41]) and the patient’s family number (variable ‘famnum’ from the patient file). Women living in household of <2 people will be classified as living alone.   - Residing in a care home (dichotomous variable: yes/no).   This variable will be defined from the CPRD GOLD primary care database, using Read codes (list provided in [41]), and information gathered in the family number variable (‘famnum’). For the latter, ‘care home’ will be defined as a household with >3 individuals aged ≥65 years and if their total count was more than of individuals <65 years.   - Ethnicity (categorical variable: White, South Asian, Black, Others and mixed)   Ethnicity data recorded in the CPRD GOLD primary care database will be categorised in five groups, following the categories defined in the UK 2011 Census: White, South Asian, Black, Others and mixed. This variable will be derived from Read codes available in the CPRD GOLD primary care database and from HES, since the combined data sources increase completeness from 55% to 79% [41]. For analysis, four groups will be considered: White, South Asian, Black, Others and mixed.   - Previous mental health history (categorical variable: yes/no)   Mental health history will be defined as having had an episode of anxiety- or depression-related disorders (primary outcomes) or any the secondary outcomes, ever recorded at more than 1 year before the breast cancer diagnosis (patients who had the outcome in the year before the breast cancer diagnosis will be excluded from the cohort). These will be identified based on the algorithms defined in aim 1 of this study.   - History of stroke or coronary heart disease at diagnosis (two dichotomous variables: yes/no)   These will include ischaemic heart disease (angina and myocardial infarction) and stroke, which are amongst the leading causes of disability-adjusted life years in females in the UK. These will be identified through Read codes recorded in the CPRD GOLD primary care database.   - Socioeconomic status (IMD quintiles of deprivation)   The IMD is an ecological measure of deprivation for small areas in England (Lower Super Output Areas). It combines information from seven domain indices (income, employment, education, health deprivation, crime, barriers to housing, and living environment). The index ranks the areas from 1 to 32,844; usually the quintiles are used for research purposes: from 1 (most deprived) up to 5 (least deprived). The IMD is linked to the primary care data using the postcode of the patient or practice. *Potential mediators of the association between breast cancer history and anxiety/depression*  - Sequelae from cancer treatments (six separate binary variables (yes/no): lymphoedema, pain, mild cognitive impairment, fatigue, sexual dysfunction, sleep disorder)   Lymphoedema will be defined using Read codes for the condition, in the CPRD GOLD primary care database. Pain, mild cognitive impairment, fatigue, sexual dysfunction, and sleep disorder are secondary outcomes of this study, and will be identified based on the algorithms defined in aim 1 of this study. Patients will be classified as having had one of these conditions if there was more than one record for these conditions within a 6-month interval.   - Exposed to endocrine treatment for breast cancer: binary variable (yes/no).   This will be defined from the CPRD GOLD primary care database using Read codes for at least two prescriptions of anastrozole, tamoxifen, exemestane, or letrozole [43] within a 6-month period. |

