| Data/ Statistical AnalysisPrimary analysesSpecific aim 1. To develop and validate algorithms to identify patients with anxiety and depression Algorithm development  A systematic review is currently under way to identify the lists of Read codes previously used to define anxiety and depression of primary care databases in the UK. The systematic review search expressions are provided in appendix 5.  *(A) Raw data tabulations*  We will estimate the number and proportion of patients recorded during the observation period with:   1. Diagnostic Read code for anxiety/depression; 2. Prescription of anxiolytics/antidepressants; 3. Referred to mental health services; 4. Symptoms of anxiety/depression.   Proportions will be estimated by calendar year.  *(B) Simpler algorithm*  We will estimate the additional contribution of prescriptions, referrals and symptoms to identify cases of anxiety/depression in CPRD. Referrals and prescriptions of anxiolytics/antidepressants will be considered as sufficient to identify cases of anxiety/depression if a Read code for symptoms of anxiety/depression, respectively, were recorded during the previous year. The reasons for this are threefold: (1) there is good evidence that GPs switched from anxiety/depression diagnostic codes to symptomatic ones [44, 45], following claims of over diagnosis of these conditions; (2) antidepressants and anxiolytics have also other indications, including anxiety disorders for antidepressants [46], which raise questions of the use of these data their own to identify these outcomes; (3) pharmacological treatment of mild depression has been discouraged since 2004 [47], and thus referrals to psychotherapy may help to capture milder cases.  *(C) Complex algorithm*  A more detailed algorithm will be developed considering that some drugs are prescribed for both depression and anxiety, in addition to manage vasomotor symptoms, which may be more frequent in breast cancer survivors than in women who did not have cancer. An example for depression is given in appendix 6. We will estimate the number of patients with anxiety/depression at each step, to evaluate how much each category adds to what has been previously recorded.  Algorithm validation  A random sample of 1 million patients of both sexes will be selected from the CPRD GOLD primary care database. We will apply each algorithm and produce descriptive statistics stratified by likelihood of having the outcome, including:   - Number and proportion of patients with the anxiety, depression or both, by 3-year calendar period; - Number and proportion of patients with the anxiety, depression or both, by 3-year calendar period, age and sex; - Number and proportion of patients with the anxiety and depression by 3-year calendar period and country in the UK.   For each outcome, we will compare the estimates obtained with others obtained from the literature, prioritising national surveys of population-based data such as the following:   - Adult Psychiatric Morbidity Survey 2007 [48] and 2014 [49]; - Measuring National Well-being programme, made available by the Office for National Statistics (includes prevalence of those in the UK with some evidence indicating depression or anxiety, since 2013, by country in the UK and English regions, and by 10-year age groups up to 75 years) [50].   The final algorithm will be chosen by considering information in the numeric value closer to the estimates obtained from the literature. Sensitivity analysis Proportion estimates considering the presence of symptomatic codes within the previous year will be re-calculated to consider shorter periods of time (i.e. 3 and 6 months). Specific aim 2. Risk of mental health outcomes in women who had breast cancer compared to women who did not have cancer**Primary outcomes analysis – depression and anxiety**Main analysis Descriptive statistics including number of events observed and person-years at risk will be computed, overall and stratified by the covariates listed in section M (see above). Medical procedures for the diagnosis of breast cancer are likely to cause anxiety. To deal with this we planned to exclude patients who had a record of anxiety diagnosed within 1 year before the breast cancer; this could result in patients with higher levels of trait anxiety being excluded from the analysis. We will calculate the number and proportion of patients who were excluded because they had the outcome in the year prior to the breast cancer, stratified by month. We will also describe how many of those who were excluded from analysis had an outcome after the breast cancer diagnosis by age-group. The quintiles of the distribution of the number of consultations (defined using the ‘consid’ variable) will be described, as this can indicate the patterns of seeking care between women with a history of cancer, compared to those who did not.  The association between breast cancer history and anxiety and breast cancer history and depression, will be quantified using Cox regression models with time since index as the underlying time scale, and stratifying on matched set to account for matching by age and primary care practice. Follow up will begin at the index date (vide section M for definition of the exposure) and will terminate when an outcome is observed. Women will be censored at the earliest date of any of these: cancer recurrence, other cancer diagnosis, death, transference out of the practice; if these events don’t occur, censoring will be observed at the date of last data collection for the practice. Crude measures of the association between breast cancer history and anxiety and depression will be reported stratifying by the covariates described in section M.  Cox multivariate regression analysis will be use to estimate hazard ratios adjusted for calendar period of breast cancer diagnosis, menopausal status, and diabetes mellitus at baseline (see list of confounders in section L, covariates, for the definition of these variables).  Interaction terms between the exposure and the following variables will be added, to explore effect modification by ethnicity (White, South Asian, Black, Others and mixed), place of residence (care home vs. household), co-habitation status (living alone vs. cohabiting), SES (quintiles of IMD), having mental health disorders history (yes vs. no), having history of stroke (yes vs. no) and coronary heart disease (yes vs. no).  Confidence intervals will be calculated using robust estimates of the standard errors, to account for the fact that patients may also contribute with time at risk in the unexposed cohort prior to their cancer diagnosis.  The proportional hazards assumption will be tested in two ways: 1) graphically, by plotting the cumulative rates on a log scale; 2) inferentially, by applying a likelihood ratio test to the estimates obtained for the entire period of observation and for time split into intervals. Sensitivity analyses Sensitivity analyses planned for this study will include a subset of patients only; this is because they use variables from linked data, which is available for a fraction of the patients only, and include variables amenable to have missing data (i.e. BMI, alcohol intake, smoking and patient-level IMD). Regarding the latter, we will quantify the completeness of each variable to decide on their inclusion in the final models. Analyses including variables with missing data will be restricted to patients with complete data for covariates (complete case analysis), if missing data is likely to be missing not a random. The following sensitivity analyses are planned:   1. The main analysis will be repeated further adjusting for age at diagnosis (continuous variable, since matching allowed for 3-year gap), patient quintile level of IMD, alcohol drinking patterns prior to index date, smoking history and body mass index categories prior to index date. 2. We will exclude women diagnosed with the outcome of interest in the year prior to the cancer diagnosis. To account for the fact that treatment for these conditions may often last for more than one year, and that mild anxiety and depression may be treated in psychological services and not result in visits to the GP, we will repeated the main analysis including only patients who had 5 years of complete follow up prior to the index date and did not have the outcome recorded at any point during this period.  Multiple comparisons We acknowledge that this study includes multiple comparisons for each outcome, and several outcomes. Thus, P-values in the range ~0.01-0.05 be considered as some statistical evidence of an effect and interpreted cautiously. Sample size considerations considering a 0.01 probability of type I error (α) are provided in see section I. Specific aim 3. To estimate association between breast cancer history and anxiety/depression by presence of lymphoedema, pain, mild cognitive impairment, fatigue, sexual dysfunction, sleep disorders, and having done endocrine therapy, during the follow up period. We will estimate the cumulative incidence and period prevalence of lymphoedema, pain, mild cognitive impairment, fatigue, sexual dysfunction, and sleep disorders, in breast cancer survivors during the overall follow up period and by 5-year of follow up period.  We will estimate the hazards of developing anxiety and depression (the main outcomes) for three groups of patients: 1) breast cancer survivors who did not develop the common complication (i.e. lymphoedema, pain, mild cognitive impairment, fatigue, sexual dysfunction, sleep disorders) up to time *t*; 2) breast cancer survivors who have had the common complication at time *t*; 3) women who never had cancer. A Cox regression model will be used to estimate the association between time-updated exposure and the main outcomes (anxiety and depression), having as reference the hazard observed for the women who did not have cancer. The exposure variable will be time-updated; this means that women who develop a common complication will contribute with information to group 1 until the date at which they develop the complication of interest; after this point they will contribute with information to group 2. All models will be adjusted for calendar period of breast cancer diagnosis.  Confidence intervals will be calculated using robust estimates of the standard errors. Sensitivity analyses planned in objective 2 will be applied to this objective as well. Secondary outcomes analyses – fatigue, mild cognitive impairment, pain, sleep disturbance, sexual dysfunction, fatal and non-fatal self-harm The steps outlined above will be repeated for the secondary outcomes. Sensitivity analysis will follow the same rationale as described for the primary analysis. |

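### Previous mental health history ignores the last year for every listed condition, but the exclusion covers only the outcome in analysis, so women with a first, recent record of another outcome are coded as having no history

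*Protocol*

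**What the plan says.** Under Exposures, Outcomes and Covariates (Potential effect modifiers), the Protocol states: "Mental health history will be defined as having had an episode of anxiety- or depression-related disorders (primary outcomes) or any the secondary outcomes". The limit on timing, with the start of the parenthesis that follows it, reads "ever recorded at more than 1 year before the breast cancer diagnosis (patients who had the outcome in the year before". The parenthesis gives the apparent reason for leaving out the final year: "patients who had the outcome in the year before the breast cancer diagnosis will be excluded from the cohort".

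The exclusion itself is stated in three places, each time for a single outcome:
- Study Design excludes women "having a history of the specified mental health outcome in the year before index date".
- Definition of the Study population, second exclusion criterion: "History of the specified mental health outcome in analysis in the year before the breast cancer diagnosis".
- Data/Statistical Analysis, Specific aim 2, second sensitivity analysis: "We will exclude women diagnosed with the outcome of interest in the year prior to the cancer diagnosis".

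Specific aim 2 uses the variable in an interaction with the exposure, listed as "having mental health disorders history (yes vs. no", and reports crude associations stratified by each covariate. The adjusted main model contains calendar period, menopausal status and diabetes. History is not in it.

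**The concern.** The variable spans all outcomes, while the exclusion that is meant to justify its one-year gap spans only one. The gap is harmless for the outcome in analysis, because women with that outcome in the last year are out. For every other listed condition, nothing removes the woman and nothing records her illness.

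The group affected is small but not random. These women have a newly recorded disorder and are plausibly at raised risk of the other primary outcome, yet they sit in the reference level. What is at stake is whether the planned interaction and the history-stratified crude results mean what their labels say. The same gap arises for the secondary outcomes, since the Protocol repeats the same analysis steps for them.

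**Working it through.** The Protocol gives no figure on this point, so there is none to reproduce. The check is to apply the written rules to each possible pattern of records.

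**Step 1: the rules applied to the anxiety analysis.** There are three yes/no facts: depression in the last year, anxiety in the last year, and any listed outcome more than 1 year before index. That makes 8 patterns. The 4 with anxiety in the last year are excluded. The other 4 are kept:

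| Depression, last year | Any listed outcome, older than 1 year | Coded history |
| --- | --- | --- |
| no | no | no |
| no | yes | yes |
| yes | yes | yes |
| yes | no | **no** |

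Only the last row is miscoded. Exchanging anxiety and depression gives the mirror case in the depression analysis.

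**Step 2: does another rule close the gap?** The severe mental illness exclusion does not list anxiety, depression or the secondary outcomes. The sensitivity analysis that requires 5 clear years before index also looks only at the outcome in analysis. If *the outcome* in the parenthesis were read as any listed outcome, it would conflict with the three statements of the exclusion. The text needs correcting on either reading.

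**Step 3: illustrative size.** Apart from the 52,335 eligible exposed women (Feasibility counts), every input here is an assumption that the Protocol does not supply.

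- Number miscoded = 52,335 × p × q, where p is the share with the other disorder in the last year (1% to 9%) and q is the share of those with no older listed record (10% to 50%). Low end: 52,335 × 0.01 × 0.10 ≈ 52. High end: 52,335 × 0.09 × 0.50 ≈ 2,355.
- Dilution of the contrast between history and no history: observed ratio = r / (1 − m + m·r), where m is the miscoded share of the no-history group and r is the true rate ratio, with miscoded women taken to carry the history rate.
  - r = 2: 2/1.01 = 1.98 at m = 1%, and 2/1.05 = 1.90 at m = 5%.
  - r = 4: 4/1.03 = 3.88 at m = 1%, and 4/1.15 = 3.48 at m = 5%.
- Effect on the exposure hazard ratio within the no-history group, with miscoding equal in both cohorts. Suppose the hazard ratio is 1.30 in correctly coded women and 1.10 in miscoded women, who have 4 times the event rate. The miscoded share of events is 4m/(1 + 3m): 0.04/1.03 = 3.9% at m = 1%, and 0.20/1.15 = 17.4% at m = 5%. Weighting by events gives about 1.30 − 0.20 × 0.039 = 1.29 and 1.30 − 0.20 × 0.174 = 1.27.
- The same hazard ratio with miscoding unequal, say 4% of exposed and 2% of unexposed no-history women. It is multiplied by (1 + 3 × 0.04)/(1 + 3 × 0.02) = 1.12/1.06 = 1.06 if their hazard is 4 times as high, and by 1.04/1.02 = 1.02 if it is twice as high. With equal shares and the same relative hazard in both cohorts, the factor is 1.00.

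**The case against.** Several objections have force.

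- **The parenthesis is not false.** It is true for the outcome in analysis. It fails only as a reason for cutting off a variable that spans all outcomes. This stands.
- **Most women with active illness may be coded correctly.** A reader might infer that any woman with active depression enters the anxiety analysis as having no history. The definition does not support that: any older record of anxiety, depression, pain, fatigue, sleep disturbance or another listed outcome makes her a yes. Because such common conditions count, the no-history group and the miscoded share may both be modest.
- **A higher event rate is not a biased hazard ratio.** With m of 1% to 5% and 4 times the hazard, the reference group's event rate rises by a factor of 1 + 3m, or 1.03 to 1.15. A reader might conclude that the interaction would be missed. The interaction compares hazard ratios, however, and similar miscoding in both cohorts largely cancels, as the 1.29 to 1.27 illustration shows. It need not cancel if miscoding differs by exposure. The Protocol itself expects the diagnostic work-up for breast cancer to provoke anxiety, and that anxiety falls in the ignored year.
- **A lag is defensible.** Extending the window to the index date would, in the depression analysis, count work-up anxiety as history mainly in women with cancer, which is miscoding that differs by exposure. This stands against the simplest remedy. It does not support leaving these women in the no-history level.
- **The use is exploratory.** History is one of seven modifiers, and the Multiple comparisons paragraph already promises caution for P-values of about 0.01 to 0.05. This lowers the priority without removing the error.

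**Conclusion.** The inconsistency is real and follows from the Protocol's text without any assumed number. It affects women whose first record of any listed condition is an outcome other than the one in analysis, made within the year before index. They are retained and coded as having no history.

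The consequence is limited to the exposure-by-history interaction and the crude results stratified by history. A reader might infer that the main adjusted hazard ratios are biased. The Protocol does not support that, since the variable is outside the adjustment set.

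The size cannot be derived from the Protocol. The baseline percentages in Table 2 come from other studies and are not presented as frequencies in the year before index, and nothing gives the share of women without an older record. The illustrations run from negligible (52 women, a ratio of 2 seen as 1.98) to noticeable (2,355 women, a ratio of 4 seen as 3.48). The within-group hazard ratio moves little unless miscoding differs by exposure. The point should be corrected before analysis, but it does not threaten the primary comparison.

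**What to change.** Code previous mental health history in three levels, separately for each outcome analysis:
1. no listed outcome before index;
2. any listed outcome more than 1 year before index;
3. first listed record, of an outcome other than the one in analysis, within the last year.

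Fit the exposure interaction and report the crude strata on these levels. Recent illness then leaves the reference group, and possible work-up anxiety in women with cancer stays apart from established history. Reword the parenthesis to say that only the outcome in analysis is excluded in the last year.

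The cost is a changed definition, a date condition in the code, and one extra category with its interaction term. That category will be smaller, so its estimate will be less precise. No patients are lost, and the main adjusted models are unchanged.
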